### **Study withdrawal**

Subjects have the right to withdraw from the study at any time and for any reason without prejudice to their future medical care by the physician or at the institution.

### **Withdrawal Criteria**

Participation of a subject in this clinical study is entirely voluntary and may be discontinued for any of the following reasons:

- The subject withdraws consent or requests discontinuation from the study for any reason;
- Occurrence of any medical condition or circumstance that exposes the subject to substantial risk and/or does not allow the subject to adhere to the requirements of the protocol;
- Any serious adverse event (SAE), clinically significant adverse event, severe laboratory abnormality, or other medical condition which indicates to the Investigator that continued participation is not in the best interest of the subject;
- Pregnancy;
- Subject failure to comply with protocol requirements or study-related procedures
- Poor compliance
- Termination of the study by the Sponsor or the regulatory authority.

If a subject discontinues prematurely from the study due to the above criteria or any other reason, study staff should make every effort to document the clinical evaluations as far as possible in the electronic case report form (eCRF).

Withdrawn subjects may not be replaced. Withdrawal of consent for a study means that the subject does not wish to receive further protocol-required therapies or procedures, and the subject does not wish to or is unable to continue further study participation.

If a participant wishes to discontinue receiving the trial interventions, they will be encouraged to remain in the study for the purposes of data collection in line with the study schedule. If they wish to discontinue data collection, they will be asked to participate in an 'end of study' assessment at the time of withdrawal. Data collected prior to withdrawal will be used in the study analysis unless consent for this is specifically withdrawn. Should a decision to withdraw from the study be made, a reason for withdrawal will be sought but participants and/or carers can choose to withdraw without providing an explanation.

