### **Investigator Responsibilities for Data Collection**

The investigator is responsible for complying with the requirements for all assessments and data collection (including subjects not receiving protocol-required therapies) as stipulated in the protocol for each subject in the study. For subjects who withdraw prior to completion of all protocol-required visits and are unable or unwilling to continue the Schedule of Assessments, the reason for the same may be acquired telephonically to the participant or the care taker and enter the same in the CRF. The PI shall ensure that the data set(s) produced as an outcome of the study is/are as comprehensive as possible.

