### **Handling of protocol violations and protocol amendments**

The nature and reasons for the protocol violation shall be recorded in the CRF, in the source documents and in the monitoring visit report. In parallel, corrective and/or preventive actions will be undertaken and documented, including any retraining of the investigator and site staff. All participants who have been included in the trial will be followed up, irrespective of whether treatment was discontinued prematurely, or whether the protocol was violated.

All important changes to the trial will be specified in protocol amendments. Amendments must be approved by the Sponsor, and the PI has the responsibility to seek approval from the competent authorities the ethics committees. The approval shall also be conveyed to the sponsor

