### ***Serious Adverse Events***

A serious adverse event is defined as an adverse event that meets at least 1 of the following serious criteria

- Results in death
- Is life-threatening (refers to an event in which the subject was at risk of death at the time of the event; it does not refer to an event which hypothetically might have caused death if it were more severe)
- Requires hospitalisation, or prolongation of existing hospitalisation
- Results in persistent or significant disability or incapacity
- Consists of a congenital anomaly or birth defect
- Is otherwise considered medically significant by the investigator

**Causality:** The assignment of the causality should be made by the investigator responsible for the care of the participant using the definitions in the table below. All adverse events judged as having a reasonable suspected causal relationship to a study procedure (i.e definitely, probably or possibly related) are considered to be related adverse events.

| Relationship   | Description                                                                                                                                                                                                                                                                                                        |
|----------------|--------------------------------------------------------------------------------------------------------------------------------------------------------------------------------------------------------------------------------------------------------------------------------------------------------------------|
| Unrelated      | There is no evidence of any causal relationship                                                                                                                                                                                                                                                                    |
| Unlikely       | There is little evidence to suggest there is a causal relationship (e.g. the event did not occur within a reasonable time after administration of the study procedure). There is another reasonable explanation for the event (e.g. the participant's clinical condition, other concomitant treatment).            |

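### The withdrawal criteria let the investigator end study participation, not only the tablets, after a safety event or poor compliance, which is at odds with the promise to follow every participant

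*Protocol*

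**What the plan says.** The protocol's Withdrawal Criteria open with "Participation of a subject in this clinical study is entirely voluntary and may be discontinued for any of the following reasons". The list that follows mixes two kinds of reason. Two do not rest on a judgement about the individual participant by the investigator: the subject's own withdrawal, and termination of the study. The others are for the investigator to act on: a medical condition or circumstance carrying substantial risk or preventing adherence, pregnancy, failure to comply with the protocol, poor compliance, and "Any serious adverse event (SAE), clinically significant adverse event, severe laboratory abnormality, or other medical condition", the last limited to one "which indicates to the Investigator that continued participation is not in the best interest of the subject".

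For anyone who leaves under these criteria or for another reason, "study staff should make every effort to document the clinical evaluations as far as possible in the electronic case report form". The section then offers more to participants who choose to stop: "If a participant wishes to discontinue receiving the trial interventions, they will be encouraged to remain in the study for the purposes of data collection". Those who wish to stop data collection as well are asked to attend a final assessment. Withdrawn subjects may not be replaced.

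Two other protocol sections bear on the same people. Handling of protocol violations and protocol amendments states: "All participants who have been included in the trial will be followed up, irrespective of whether treatment was discontinued prematurely", and extends this to participants for whom the protocol was violated. Investigator Responsibilities for Data Collection makes the investigator responsible for "all assessments and data collection (including subjects not receiving protocol-required therapies) as stipulated in the protocol for each subject in the study", while accepting that some subjects will withdraw and be unable or unwilling to continue.

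**The concern.** The withdrawal list acts on participation in the study, whereas the follow-up promise treats stopping the tablets and leaving the study as different things. An investigator who takes a participant off study after an adverse event, or for poor compliance, acts within the first section and breaks the second. The text available does not say which governs.

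Safety is part of the primary objective, and it is to be judged on all adverse and serious adverse events during the study. The primary outcome is the change in LDL from baseline to 12 weeks. Statistical analyses names the intention-to-treat principle and says that missing data will not be imputed. Observations that stop because of an event or poor compliance are not missing at random with respect to safety or efficacy. If tolerability or compliance differs between Trikatu and placebo, the losses can differ by arm too. A statistical analysis plan cannot bring back data that were never collected.

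**Working it through.** No figure in the protocol underlies this point. The check sets the sections side by side and then gauges scale.

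1. What the rule acts on. The opening of Withdrawal Criteria refers to participation in the study, and the later sentence on documentation speaks of subjects leaving the study because of the criteria. The rule is therefore not confined to the tablets.

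2. How strong the rule is. It is permissive. The bullet on adverse events and laboratory abnormalities also depends on investigator judgement. The pregnancy and compliance bullets carry no such qualifier but stand under the same permissive opening.

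3. What is secured afterwards. When the participant wishes to stop the intervention, remaining for data collection is encouraged. When the participant wishes to stop data collection, a final assessment is requested. When the investigator decides, only documentation as far as possible is asked for, with no statement that scheduled visits continue.

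4. Comparison with the follow-up rules. The section on protocol violations promises follow-up of all included participants. Its clause on violations is hardest to square with the two compliance bullets, because poor compliance is a departure from the protocol for which participation may nevertheless be ended. The data-collection section requires assessments off treatment. Its exception covers people unable or unwilling to go on, and a participant removed by the investigator need be neither.

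5. What can be lost. In the Schedule of Assessments, LFT, RFT and CBC fall at screening and Day 84 only. A participant taken off study before Day 84 may therefore have no scheduled safety laboratory result on treatment. Lipids are scheduled at screening and Days 28, 56, 84 and 112, so early values may exist, but the 12-week LDL that defines the primary outcome would be absent. Adverse events arising after the exit would have no scheduled visit at which to be captured.

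6. Scale. From Sample Size and statistical considerations, the stated evaluable number reproduces: (30² + 30²) × (1.96 + 0.84)² / 14² = 1,800 × 7.84 / 196 = 72 per group. With 85 enrolled and 20% lost, 85 × 0.80 = 68 remain, at which power for 14 mg/dl with SD 30 is 77.7%. This is background only: the planned allowance leaves no slack for avoidable losses. Planned attrition overall is 0.20 × 170 = 34. The protocol does not say what share would be investigator-initiated. Assuming 10% to 50%, the number is 3.4 to 17, or about 3 to 17. In a safety table one participant is 1/85 = 1.2 percentage points of an arm.

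**The case against.** The strongest reply is that the withdrawal list is permissive, so an investigator can satisfy every section by never using the list to end follow-up. A reader might infer that participation stops automatically at a serious adverse event, or that the sections cannot both be applied. The text supports neither reading. The data-collection section also accepts withdrawals, so the clear conflict is with the section on protocol violations. All of this stands and limits the point, but it does not remove it: the list still permits what the other section rules out.

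Second, there are safeguards. The effort to document applies to every premature discontinuation, and Recording and reporting of serious adverse events asks for dates of onset and resolution, with no exemption for people who have left. The triggering event would be recorded and counted. This also stands. What remains exposed is later events and the Day 84 measurements.

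Third, because one seriousness criterion reads "Consists of a congenital anomaly or birth defect", a reader might infer that ending participation at pregnancy makes that outcome unobservable. This does not follow. The last visit is Day 112, and women who are pregnant or planning pregnancy are excluded, so the outcome of a pregnancy begun on study would normally fall after the last visit whether or not participation ended.

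Finally, parts of the protocol are not in the available text, so a further rule on following adverse events cannot be ruled out. The visible conflict would still need to be settled.

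**Conclusion.** The point holds in a limited form. Withdrawal Criteria permit, but do not require, an investigator to end study participation for medical reasons, pregnancy, failure to comply or poor compliance, and secure only best-effort documentation when that happens. This does not fit the promise to follow all included participants or the requirement for assessments off treatment. Where the discretion is used before Day 84, later safety data, the Day 84 LFT, RFT and CBC, and the 12-week LDL can be lost in a way that depends on events or compliance. That works against the stated intention-to-treat principle, and no imputation is planned.

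The size cannot be derived from the protocol. The range of about 3 to 17 of 170 rests wholly on an assumed 10% to 50% share of the planned attrition. It is a scale for the problem, not an estimate of loss or bias. The direction of any bias is unknown, since it depends on how events and compliance differ between arms.

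**What to change.** Reconcile Withdrawal Criteria with Handling of protocol violations and protocol amendments and with Investigator Responsibilities for Data Collection:

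- State that the investigator-initiated reasons, including both compliance bullets, do not by themselves end data collection.
- State that scheduled visits to Day 112 and recording of adverse events continue unless the participant withdraws consent to follow-up or the study is terminated.
- Record separately, with date and reason, stopping the intervention and leaving follow-up, and report both numbers by arm.

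Which events lead to stopping the tablets, and any rule for following pregnancies, are for the sponsor to decide.

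This is a cheap improvement: one protocol paragraph and a few CRF fields, using visits already scheduled. The small downside is continued visits or contacts for a few participants who are off treatment.

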### **Trial conduct and practices/procedures:**

### **Compliance with regulations and guidelines:**

The trial will conform to the National Ethical Guidelines for Biomedical and Health Research Involving Human Participants (2017) ICMR and Good Clinical Practice guidelines for Clinical Trials in Ayurveda, Siddha and Unani Medicine (GCP-ASU), 2013.

#### **Informed Consent:**

Before a participant's participation in the clinical study, the investigator is responsible for obtaining written informed consent from the participant after adequate explanation of the aims, methods, anticipated benefits, and potential hazards of the study and before any protocol-specific screening procedures or any investigational product(s) is/are administered.

The acquisition of the informed consent and the participant's agreement or refusal is to be documented in the participant's medical records, and the informed consent is to be signed and personally dated by the participant and by the person who conducted the informed consent discussion. The original signed informed consent is to be retained in accordance with the CCRAS Research Policy, and a copy of the signed consent form is to be provided to the participant.

If a potential participant is illiterate or visually impaired and does not have a legally acceptable representative, the investigator must provide an impartial witness to read the informed consent to the participant and must allow for questions. Thereafter, both the participant and the witness must sign the informed consent to attest that informed consent was freely given and understood.

#### **Institutional Ethics Committee:**

A copy of the protocol, proposed informed consent, other written subject information, and any proposed advertising material must be submitted to the IEC for written approval. A copy of the written approval of the protocol and informed consent must be received by the CCRAS before recruitment of subjects into the study.

The investigator must submit and, where necessary, obtain approval from the IEC for all subsequent protocol amendments and changes to the informed consent. The investigator is to notify the IEC of deviations from the protocol or serious adverse events occurring at the site.

#### **Study Documentation and Archive**

The investigator is to maintain a list of appropriately qualified persons to whom he/she has delegated study duties. Source documents are original documents, data, and records from which the subject's CRF data are obtained. These include but are not limited to hospital records, clinical and office charts, laboratory and pharmacy records, diaries, and correspondence. CRF entries may be considered source data if the CRF is the site of the original recording (ie, there is no other written or electronic record of data).

The investigator and study staff are responsible for maintaining a comprehensive filing system of all study-related (essential) documentation, suitable for inspection at any time by representatives from CCRAS and/or applicable regulatory authorities.

The documents shall include:

- Subject files containing completed CRFs, informed consents, and subject identification list
- Study files containing the protocol with all amendments, Investigator's Brochure, , and all correspondence to and from the IEC and CCRAS

In addition, all original source documents supporting entries in the CRFs must be maintained and be readily available.

### **Data protection:**

Personal identifiers will not be stored together with clinical information about the participant, but will be stored on a separate, password-protected computer with access only for persons in the Trial centre/ statistics unit who are responsible for data analysis. The code linking personal identifiers with clinical data will be destroyed 15 years after the publication of the primary report, of the trial.

### **Participant Confidentiality**

The investigator must ensure that the participants confidentiality is maintained for documents submitted.

- Participants are to be identified by a unique identification number.
- For serious adverse events reported, participants are to be identified by their unique participant identification number, initials and date of birth (in accordance with local laws and regulations).
- Documents that are not submitted to (eg, signed informed consent s) are to be kept in confidence by the investigator, except as described below.

In compliance with the Good Clinical Practice (GCP) Guidelines, it is required that the investigator and institution permit authorized representatives of the sponsor, of the regulatory agency(s), and the IEC direct access to review the original medical records for verification of study-related procedures and data. Direct access includes examining, analysing, verifying, and reproducing any records and reports that are important to the evaluation of the study. The investigator is obligated to inform and obtain the consent of the participant to permit such individuals to have access to his/her study-related records, including personal information.

### **Study Monitoring and Data Collection**

The CCRAS representative(s) and regulatory authority monitors can visit the investigator for the purpose of inspecting the facilities and, upon request, inspecting the various records of the clinical study (eg, CRFs and other pertinent data) provided that subject confidentiality is respected.

The Clinical Monitoring committee is responsible for verifying the CRFs at regular intervals throughout the study to verify adherence to the protocol; completeness, accuracy, and consistency of the data; and adherence to local regulations on the conduct of clinical research. The Clinical Monitoring committee is to have access to subject medical records and other study-related records needed to verify the entries on the CRFs. The investigator shall cooperate with the Clinical Monitoring committee to ensure that any problems detected in the course of these monitoring visits, including delays in completing CRFs, are resolved.

- Data capture for this study is planned to be in both hard copies of CRF and electronic format
- All source documentation supporting entries into the CRFs must be maintained and readily available
- To ensure the quality of clinical data across all subjects, clinical data management review is performed on subject data received at CCRAS. During this review, subject data are checked for consistency, omissions, and any apparent discrepancies. In addition, the data are reviewed for adherence to the protocol and GCP.

### **Investigator Responsibilities for Data Collection**

The investigator is responsible for complying with the requirements for all assessments and data collection (including subjects not receiving protocol-required therapies) as stipulated in the protocol for each subject in the study. For subjects who withdraw prior to completion of all protocol-required visits and are unable or unwilling to continue the Schedule of Assessments, the reason for the same may be acquired telephonically to the participant or the care taker and enter the same in the CRF. The PI shall ensure that the data set(s) produced as an outcome of the study is/are as comprehensive as possible.

### **Handling of protocol violations and protocol amendments**

The nature and reasons for the protocol violation shall be recorded in the CRF, in the source documents and in the monitoring visit report. In parallel, corrective and/or preventive actions will be undertaken and documented, including any retraining of the investigator and site staff. All participants who have been included in the trial will be followed up, irrespective of whether treatment was discontinued prematurely, or whether the protocol was violated.

All important changes to the trial will be specified in protocol amendments. Amendments must be approved by the Sponsor, and the PI has the responsibility to seek approval from the competent authorities the ethics committees. The approval shall also be conveyed to the sponsor

### **Safety data collection, recording, and reporting:**

Clinical trials provide the evidentiary basis for regulatory approvals of safe and effective interventions. The safety of the trial intervention, will be evaluated by examining the occurrence of all adverse events and serious adverse events during the course of the study.

### **Definitions**

**Adverse event (AE):** Any untoward medical occurrence in a participant to whom a study intervention or procedure has been administered, including occurrences which are not necessarily caused by or related to that intervention. An AE, therefore, does not necessarily have a causal relationship with the treatment. In this context, "treatment" includes all interventions (including comparative agents) administered during the course of the study. The definition of adverse events includes worsening of a pre-existing medical condition. Worsening indicates that the pre-existing medical condition or underlying disease (eg, diabetes, migraine headaches,) has increased in severity, frequency, and/or duration more than would be expected, and/or has an association with a significantly worse outcome than expected.

